## Abstract

(1) Background: We present the protocol of a randomized controlled trial designed to evaluate the benefit of a novel clinical decision support system for the management of patients with COVID-19. (2) Methods: The study will recruit up to 500 participants (250 cases and 250 controls). Both groups will receive the conventional telephone follow-up protocol by primary care and will also be provided with access to a mobile application, in which they will be able to report their symptoms three times a day. In addition, patients in the active group will receive a wearable smartwatch and a pulse oximeter at home for real-time monitoring. The measured data will be visualized by primary care and emergency health service professionals, allowing them to detect in real time the progression and complications of the disease in order to promote early therapeutic interventions based on their clinical judgement. (3) Results: Ethical approval for this study was obtained from the Drug Research Ethics Committee of the Valladolid East Health Area (CASVE-NM-21-516). The results obtained from this study will form part of the thesis of two PhD students and will be disseminated through publication in a peer-reviewed journal. (4) Conclusions: The implementation of this telemonitoring system can be extrapolated to patients with other similar diseases, such as chronic diseases, with a high prevalence and need for close monitoring.

## 1. Introduction

In late December 2019, a number of cases of severe illness and death caused by Acute Respiratory Distress Syndrome (ARDS) were reported in Wuhan, China. The causative agent of these events was identified as Severe Acute Respiratory Syndrome Coronavirus 2 (SARS-CoV-2), which would later be responsible for the pandemic that has paralyzed the world for almost 2 years [1]. Since its outbreak, the coronavirus disease 2019 (COVID-19) has infected more than 640 million people and has resulted in 6.6 million deaths [2]. Spain has been one of the ten countries with the highest infection rate in the world; of a population of 47.5 million, around 13.5 million people were infected and 5000 individuals lost their lives due to the disease [2]. This high morbidity and mortality has been reduced with the vaccination of the population [2].

The most common symptoms of COVID-19 include fever, cough, headache, fatigue and gastrointestinal symptoms [3,4,5]. On the other hand, the main complication of the disease is ARDS, which appears as a consequence of the cytokine storm released in response to the infection. This condition is associated with a mortality ranging from 26% to 61.5% if admitted to a critical care setting and 65.7% to 94% in patients who received mechanical ventilation [6]. In this regard, the LUNG-SAFE study revealed that approximately 50% of mild ARDS goes undetected, with a probability of progression to moderate–severe ARDS of 40% and an in-hospital mortality rate of 30% [7,8]. Thus, the early detection of clinical worsening of COVID-19, manifested as ARDS or other potential serious complications, would allow for timely therapeutic interventions that would improve the health outcomes of these patients [9]. It should be noted that, in comparison with the first pandemic wave in early 2020, these figures have been significantly reduced by vaccination of the population, the emergence of variants with higher transmission but lower mortality rates and improved therapeutics for the disease [10].

As COVID-19 has a very broad clinical spectrum, the monitoring of the body temperature (BT), heart rate (HR), respiratory rate (RR), blood pressure (BP) and oxygen saturation (SatO2) may contribute to the early detection of clinical worsening or the occurrence of any major complications. For example, the risk of respiratory failure in the first 24 h after hospital admission based on the Quick COVID-19 Severity Index can be predicted by monitoring SatO2 and RR [11]. Similarly, alterations in certain vital signs such as BT (≥38 °C), RR (≥20 breaths per minute) and HR (>100 beats per minute) can help identify the existence of pneumonia among adult patients in primary care settings [12].

With this in mind, most studies within this line of research have used different devices to monitor each vital sign in isolation [13,14], with only a few assessing several parameters simultaneously. The latter includes one by Chung et al. [15] that used the HEARThermo device for continuous monitoring of BP and HR in patients with suspected or confirmed COVID-19 and another by Chinitz et al. [16] that used the Apple Watch Series 4 (Apple, Cupertino, CA, USA) to monitor arrhythmias and QT prolongation in COVID-19 patients in home quarantine. In addition, most of the devices that have been used for early detection of COVID-19 have been tested outside Europe [14,15,16,17,18].

One purpose of the protocol is to serve as a model for similar studies under similar conditions in order to improve pathology control. We propose to evaluate the benefit of a clinical decision support system based on: (i) the self-reporting of patient symptoms through a mobile application and (ii) the processing of data measured by wearable monitoring devices using artificial intelligence techniques in patients with COVID-19 in quarantine. All data generated will be uploaded to an online platform to which access will be provided to primary care and emergency health service professionals, allowing real-time detection of the progression of COVID-19 to severe forms and the occurrence of any potential major complications in order to promote early therapeutic interventions based on their clinical judgement. It is hypothesized that the implementation of the proposed clinical decision support system will improve the rate of detection of the clinical progression to severe forms of the disease in COVID-19 positive patients in home quarantine, compared to current practice.

The study will examine the differences between the active and control groups 30 days after the date of diagnosis of COVID-19, in terms of clinical progression of the disease to severe forms, defined by: progression to pneumonia, need for intensive care unit (ICU) admission, need for invasive mechanical ventilation and mortality rate. On the other hand, the secondary outcomes to be considered will be: the hospital admission rate, the average hospital stay, the occurrence of major vascular events (including acute myocardial infarction, stroke and vascular death), the economic cost of the derived care to the health system, the satisfaction of professionals and patients with the project and the usability of the technologies used in the project.

## 2. Materials and Methods

### 2.1. Study Design

Prospective, single-blind, multicenter, randomized clinical trial. Acute COVID-19 included study patients will be randomized to one of both study arms: conventional telephone calls from healthcare professionals, periodic telemonitoring with wearable devices and mobile phone application allowing self-reporting of symptoms three times a day versus traditional telephone calls from healthcare professionals and symptom reporting application.

### 2.2. Eligibility Criteria

To be considered for participation in the study, patients must meet all the inclusion criteria set out in this protocol without meeting any exclusion criteria (Table 1).

All patients participating in the study will receive an SMS message on their mobile phone with a link to download the healthcare app, from which they will initially electronically sign the informed consent form required to participate in the study (Supplementary Materials, File S1) and provide their contact details and home address for delivery of the Bakeey E66 smartwatch and Wellue FS20F pulse oximeter, if randomly assigned to the active group.

When patients are discharged and their home quarantine period ends, after seven or ten days depending on symptomatology, they will be able to remove the healthcare application called ‘‘Home app’’ from their mobile phone and stop wearing the monitoring devices, although their participation in the study will not end until six months after the date of the positive PCR or antigen test, when they will receive a final follow-up call from the data monitoring board to assess the primary and secondary outcome measures.

### 2.3. Setting

Patients will be recruited from the two health areas of Valladolid (total target population: 560,000 habitants). The primary care centers that have been selected by the Technical Direction of Primary Care in both areas are: from Valladolid East Health Area, the centers Barrio España, Cabezón de Pisuerga, Canterac, Cigales, Circunvalación, Gamazo, Iscar, Magdalena, Medina del Campo, Olmedo, Pilarica, Portillo, Renedo de Esgueva, Rondilla, San Isidro, Santovenia and Tudela de Duero; from the Valladolid West Health, the following centers: Area Arturo Eyries, Casa del Barco, Covaresa, Delicias, Huerta del Rey, La Cistérniga, Parquesol and Plaza del Ejército. Furthermore, the Health Emergency Service of Castilla y León will participate, managing and responding to the serious alerts produced by the platform.

### 2.4. Sampling

For the sample size calculation, the population of COVID-19 patients in the province of Valladolid during the 6-week period, November–December 2021 (3210 potential patients) is used as a frame. Conversely, for the calculation of the sampling error, the worst-case scenario of *p* and q = 0.50 and a confidence level of 1.96 was considered.

The consecutive sampling of all COVID-19 patients who meet the eligibility criteria will be conducted for a period of six weeks. The contact details of all patients who electronically sign the informed consent form required to participate will be recorded so that they can be contacted in six months for a follow-up call.

To ensure an equitable and randomized allocation of patients to one or the other study group, an automatic selection table will be used according to the number assigned to each patient in the study, consisting of three numerical digits indicating the consecutive order of inclusion (001, 002, 003, etc.). This selection table will be obtained by generating 500 random numbers so that each random number generated will be a case, and the rest will be a control. In this way, the process will end when 250 numbers (cases) are generated.

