### 2.7. Data Analyses Plan

A professional biostatistician has been consulted to design the data analysis plan for the study, in which descriptive analysis of all data will be provided, including means and SDs or medians for continuous variables and proportions for categorical variables. The recorded data will be processed statistically in an encrypted form.

The statistical analysis technique to be used will be the analysis of variance (ANOVA), which will allow determining the existence of significant differences between the two groups in terms of primary and secondary outcome measures. Also, the Kaplan–Meier estimator and Cox proportional hazards model will be used to establish possible predictors of mortality and/or ICU admission. The statistical software to be used will be Stata 15 and a *p*-value of <0.05 will be assumed for statistical significance.

To assess the economic impact of the intervention on the health and social system, a cost-utility analysis will be carried out to evaluate whether there are fewer hospitalizations and calls to the emergency health service in the active group than in the control group, which translates into lower costs associated with patient care. With this in mind, an acceptability curve analysis will be carried out to see whether the proposed clinical decision support system is more appropriate than the conventional primary care telephone follow-up in terms of cost-benefit ratio.

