This device will also allow the detection of alarm symptoms in real time and trigger a health alert for early attention in case of clinical progression of the disease or the appearance of a serious complication. Similar monitoring systems can identify patients in need of further testing, prioritizing the use and allocation of resources [21,32]. In turn, the proposed system will provide clinical decision support to primary health care professionals, reducing complications, the length of hospital stays and the negative impact on short- and long-term health. The comprehensive and individualized monitoring of the most vulnerable patients with COVID-19, such as those over 60 years of age, people with risk factors such as hypertension, diabetes, cardiovascular disease or cancer, will be possible [32].

Morbidity and mortality and the complications of the COVID-19 disease have decreased exponentially due to the mass vaccination of the population, but the clinical benefits expected from the provision of this follow-up could be extrapolated to patients with other diseases requiring multimodal, continuous and non-invasive telemonitoring. For example, patients with analogous conditions with other diseases, such as people with chronic pathologies requiring comprehensive monitoring, after an acute event such as a stroke or for the monitoring of the most vulnerable individuals. This system would promote real-time health monitoring through virtual triage that classifies each patient according to their symptomatology and vital signs, so that interventions or treatments are more appropriate to the characteristics of each patient. In addition, the amount of data collected would help to study and combat current and future outbreaks, discover digital biomarkers, health indicators for diagnosis and quantification of health conditions.

In addition, the study aims to address the problem of geographical dispersion present in our community [33], with the understanding that technology should serve to accommodate and provide healthcare support to people living in both urban and rural areas. The main beneficiaries of this system will be patients living in rural areas with difficult access to health services or with risk factors for worsening COVID-19 due to coexisting conditions such as hypertension, diabetes or oncological processes.

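### Section 2.4 sizes the trial with a one-sample survey margin at p = 0.50, which does not justify a randomised comparison of 250 with 250 patients

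*Protocol article*

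**What the plan says.** Section 2.4 (Sampling) introduces its sample size calculation with the COVID-19 patients of Valladolid province over six weeks in late 2021: "3210 potential patients) is used as a frame". It then turns to a sampling error: "Conversely, for the calculation of the sampling error, the worst-case scenario of" p and "q = 0.50 and a confidence level of 1.96 was considered". The justification stops there.

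The Abstract gives the size: "The study will recruit up to 500 participants (250 cases and 250 controls").

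The Introduction sets the aim as a comparison of the active and control groups at 30 days on progression to severe disease, defined by pneumonia, ICU admission, invasive ventilation and death. Section 2.7 (Data Analyses Plan) tests group differences, with the rule that a p-"value of <0.05 will be assumed for statistical significance".

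On event frequency, the Discussion says: "Morbidity and mortality and the complications of the COVID-19 disease have decreased exponentially". The Limitations expect 80–85% of the city's population to have two vaccine doses at the start of the study. Table 1 excludes patients whose disease has already progressed significantly before inclusion.

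**The concern.** A population frame, a sampling error, p = q = 0.50 and 1.96 together describe how precisely one percentage would be estimated by surveying a known population. They contain no control-arm risk, no difference between arms and no power. The trial's question is about a difference between two randomised arms, which a margin for one pooled proportion does not describe.

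Calling p = 0.50 the worst case adds to the problem. It is the worst case for the absolute width of an interval around a proportion. It is not a cautious choice for detecting a relative reduction in an uncommon event, and the article's own remarks on vaccination and its exclusion criteria point to uncommon events.

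What is at stake is interpretation. A reader may take 500 as a size justified for the comparison, and may then read a non-significant result on ICU admission, ventilation or death as absence of benefit when the trial had little chance of showing one. The Introduction also offers the protocol as a model for similar studies, so the reasoning may be copied.

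**Working it through.** **Inputs from the article.** Frame N = 3210, p = q = 0.50 and z = 1.96 (section 2.4); up to 500 patients, 250 per arm (Abstract); significance at 0.05 (section 2.7). Sidedness is not stated; two-sided is assumed, which matches 1.96. No margin, control risk or target difference is printed.

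**Step 1: can 500 be reproduced?** Not from the printed inputs alone, because the margin e is missing. The survey formula is n = N z²pq / [e²(N − 1) + z²pq], with z²pq = 3.8416 × 0.25 = 0.9604.

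- e = 3%: 3082.9 / (2.888 + 0.960) = 801.1, so 802
- e = 4%: 3082.9 / (5.134 + 0.960) = 505.8, so 506
- e = 5%: 3082.9 / (8.023 + 0.960) = 343.2, so 344

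Without the finite-population correction, e = 4% needs 601. Working back from n = 500:

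- with correction: 1.96 × √(0.25/500 × 2710/3209) = 4.03 points
- without: 1.96 × √(0.25/500) = 4.38 points

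A margin of about 4 points is therefore a plausible origin of 500, but it is an inference.

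**Step 2: precision of the contrast the trial will estimate.** The 95% half-width of a difference between two arms of 250 at common risk p is 1.96 × √(2p(1 − p)/250). At p = 0.50 this is 1.96 × √(0.5/250) = 8.77 points. That is exactly twice the uncorrected survey margin and 8.77/4.03 = 2.2 times the corrected one.

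**Step 3: power for the comparison.** The test is the two-proportion z test, two-sided 0.05, with pooled variance under the null:

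power ≈ Φ{[(p₁ − p₂) − 1.96 × √(2p̄(1 − p̄)/250)] / √([p₁(1 − p₁) + p₂(1 − p₂)]/250)}

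Example, 10% v 5%: (0.05 − 1.96 × 0.02356)/0.02345 = 0.163, giving 56.5%.

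The control risks below are assumptions.

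| Assumed control risk | 95% half-width if both arms share it (points) | Smallest reduction with 80% power | Power to halve the risk |
|---|---|---|---|
| 20% | 7.0 | to 11.0% | 88% |
| 15% | 6.3 | to 7.15% | 76% |
| 10% | 5.3 | to 3.7% | 56% |
| 5% | 3.8 | to 0.8% | 31% |
| 2% | 2.5 | needs an exact method | 15% |

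The normal approximation is rough in the last two rows.

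**Step 4: is p = 0.50 cautious?** Halving from 50% to 25% gives (0.25 − 1.96 × 0.0433)/0.0418 = 3.95, a power above 99.9%. The same relative effect from 5% has 31%. For a relative reduction, 0.50 is far more favourable than a low rate.

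**The case against.** The strongest reply is that this is a condensed article and the full protocol may contain a power calculation. That cannot be excluded, and the absence of power, effect size or dropout is not itself the point. The point is what the article does state: a basis for the sample size that belongs to a different design. A calculation elsewhere would not make this paragraph correct.

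Second, the article prints neither a 4% margin nor a finite-population correction, and never expressly derives 500 from its inputs. This stands. No arithmetic in the article is shown to be wrong; the fault is a mismatch between the stated basis and the aim.

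Third, no rate is given for pneumonia or for progression overall. This also stands. At a control risk of 20%, power to halve the risk is 88%, so a reader should not infer that the main outcome is shown to be badly underpowered.

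Other stronger readings are tempting but unsupported:

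- *At 3% or less, even complete elimination could not be shown.* The normal formula gives 79.0% at 3%, but it fails with so few events. On the pooled test, 4 v 0 events already gives p = 0.045, so exact power against elimination is 94% at 3% and 74% at 2%. Fisher's test gives 76% at 3%. The answer depends on the test.
- *p = 0.50 is the most favourable value possible.* Power for a fixed relative reduction keeps rising above 50%.
- *The pandemic counts in the Introduction forecast deaths in the trial.* They are whole-population ratios, not figures for selected, mostly vaccinated home patients.
- *The survival models are over-fitted multivariable models.* Section 2.7 says only that the methods "will be used to establish possible predictors of mortality and/or ICU admission". It does not say multivariable.

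**Conclusion.** The sample size basis in section 2.4 is wrong as written for this trial. It is a one-sample survey calculation, and it does not justify a randomised comparison of 250 with 250. The mismatch itself rests only on the article's text. The between-arm half-width at p = 0.50 is 8.8 points, against an inferred survey margin of 4.0 to 4.4.

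The power shortfall rests on assumed control risks and a two-sided 0.05 test. Power to halve the risk is below 80% at assumed control risks of 15% and lower. That such low risks apply to ICU admission, ventilation and death is a reasonable reading of the article's own remarks, but it gives no rate. For pneumonia and overall progression the question stays open. Nor does the article say that a null result would be reported as no benefit; that is a risk of misreading, not a stated plan.

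**What to change.** In section 2.4, remove the survey-margin reasoning and the description of p = 0.50 as a worst case. For the fixed 250 + 250, state:

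- the 95% half-width of the between-arm difference and the smallest difference detectable with 80% power, across control risks labelled as assumptions (for example 2% to 20%), with sidedness stated and an exact method at the low rates;
- that ICU admission, invasive ventilation and mortality will be reported as between-arm differences with confidence intervals, and that a non-significant result on them is not evidence of no effect.

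The 3210 patients can stay as a description of the recruitment pool, but not as a term in the sample size.

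The cost is protocol wording and a short calculation. No more patients are needed. The drawback is that the stated justification becomes less favourable.

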### 2.5. Study Overview

#### 2.5.1. Clinical Decision Support System

The clinical decision support system to be evaluated will supplement the conventional follow-up telephone call provided by primary care to COVID-19 patients (Supplementary Materials, File S2) and will consist of the following elements.

The healthcare application called ‘‘Home app’’: all patients who meet the eligibility criteria and consent to participate will be provided with access to the ‘‘Home app’’, which they can download via SMS to their mobile phone. Importantly, this application will only be compatible with smartphones running an Android^®^ operating system (Google, Mountain View, CA, USA). The application will send push notifications to the patient three times a day (10:00 a.m., 4:00 p.m., 10:00 p.m.), asking them to indicate the presence of COVID-19 related symptoms and their characteristics, and will serve as a link for sending the vital signs data measured by the wearable monitoring devices to the server, where they will be further processed using artificial intelligence techniques (only in the active group). The symptomatology covered by the ‘‘Home app’’, together with the series of clinical questions associated with each symptom, are listed in Figure 1.

Wearable monitoring devices: patients randomly assigned to the active group will receive, at home by express courier, the Bakeey E66 smartwatch (Shenzhen Yisi Technology Co. Ltd., Guangdong, China), for real-time monitoring of BT, HR and RR, and the FS20F Bluetooth Finger Oximeter (Wellue, Los Angeles, CA, USA), for self-reporting SatO2 values three times a day via the healthcare application (along with self-reporting of symptoms). Instructions will be provided to link participants, via Bluetooth, with the healthcare application and to send the monitored data to a server where it will be further processed using artificial intelligence techniques, generating moderate or severe alerts depending on whether they exceed certain pre-established values. Whenever an alarm is detected, a push notification will automatically be sent to the healthcare application, where the patient will have to answer a series of verification questions to confirm the veracity of the alarm (Figure 2).

Online platform: both the data measured by the wearable monitoring devices and the data self-reported by patients in the ‘‘Home app’’ will be uploaded to an online platform. and record that will be accessed daily by the primary care and emergency health service professionals who wish to participate in the study. Specifically, primary care professionals will be responsible for the management of moderate alarms and emergency health service professionals will be responsible for the management of severe alarms, being alerted of their existence through a computer-generated voice message. Participating healthcare professionals will have to register on the same platform and act in response to each alarm according to their clinical judgement. This will allow the research team to monitor the management of the different alarms generated throughout the study. In this way, the platform will not only serve as a clinical data registry to guide decision-making on the management of COVID-19 patients in home quarantine by both primary and specialized care, but will also serve as a repository of data that can be made available to public health agencies or even other researchers upon reasonable request (Figure 3).

Integration of the system modules: Regarding primary care, health professionals (nurses and doctors) will be responsible for recruiting patients. At first, the screening will be carried out on the online platform which will coincide with the first call of the conventional protocol, where it will be assessed if the patient meets the inclusion and exclusion criteria. If the patient meets the inclusion and exclusion criteria, the system will allow the baseline visit to be made, which will coincide with the first call after the patient is diagnosed with COVID-19. Data from the initial visit will be recorded, the new patient will be registered with an associated mobile phone number and an anonymous and unique ID will be provided. The online platform itself will randomly assign the patient to the case or control group. At that point, a message will be sent to activate the patient. Once the user opens the message, they will have to click on the link to download the health application called ‘‘Home app’’ where they will fill in their data, receive information about the project and data processing and sign the informed consent if they agree. In the case of the active group, a request will be sent, with the delivery address of the bracelet, to the transport company that previously arranged the shipment of the devices. Once the patient receives the bracelet, they will link the bracelet to the application and if they need support, they will receive it either via telephone call, which will be available for 14 h a day, or in the application itself. Healthcare professionals will be able to record on the web panel the registered telephone calls made according to the current protocol, the vital signs will be displayed in real-time, the responses that will be provided three times a day from patients on their perceived clinical state, and the alerts issued by the alteration of any parameter. In the event of a serious alarm, it will be received by the emergency system to provide immediate care, if required by the patient. At the end of the monitoring period, the primary health care staff will discharge the patient. In the case of the active group, the logistics will be activated to collect the devices and take them to a disinfection point. In addition, to improve the healthcare support system, a satisfaction survey and a usability survey will be carried out among patients and healthcare professionals who have participated in the study.

Patient and health professional support: the clinical decision support system (the application and wearable monitoring devices) is designed to make it easy for the patient to use, to promote patient autonomy, to make the user the center of the disease and to provide individualized health care. The application is very intuitive and the collection of vital signs will be carried out automatically, it is only necessary for the patient to have the devices in place. In case the patient needs technological support, a family member could, if desired, help to answer questions about the evolution of the development of the disease and manage the placement of the monitoring devices. In addition, patients will have access to a remote support system fourteen hours a day, via telephone contact or through an online chat in the application itself. The objective of providing remote support by qualified personnel is to promote greater patient and caregiver adherence. Furthermore, this support system can also be used by healthcare professionals to improve system management. It should be noted that the application will have a section of frequently asked questions, which will be updated and new ones will be added depending on the problems reported by patients and professionals, which will be answered employing infographics in very simple language, to favor the autonomy of the user and the healthcare professional.

Machine learning models will be used to implement the system and manage the data. To start with, the raw data from the wristbands will be calculated using the median of 5 min of monitoring constants, then new columns will be created to identify if there are anomalies, what type of alert it is (medical or technical), what type of parameter it measures and the level of alert (mild, moderate and severe). The selection of these columns will be based on clinical judgment and will define when an alert is sent. In order to generate predictions based on the best model to classify future patient alerts, different models will be implemented and the one that produces the least possible false positives and best fits the data flow of the system will be selected. In total, thirteen models will be implemented: Random Forest Classifier, Gradient Boosting Classifier, Ada Boost Classifier, Extra Trees Classifier, Decision Tree Classifier, Light Gradient Boosting Machine, K Neighbors Classifier, Naive Bayers, Quadratic Discriminant Analysis, Ridge Classifier, Linear Discriminant Analysis, Logistic Regression, SVM- Linear Kerner.

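### The described workflow allocates the arm before in-app information and signed consent, conflicts with other sections on this order, and leaves room for arm-dependent loss after allocation

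*Protocol article*

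**What the plan says.** The paragraph on integration of the system modules in section 2.5.1 sets out the recruitment sequence. Primary care staff screen the patient on the platform during the first call, "where it will be assessed if the patient meets the inclusion and exclusion criteria". An eligible patient has the baseline visit: "Data from the initial visit will be recorded, the new patient will be registered with an associated mobile phone number", and an ID is issued. Next, "The online platform itself will randomly assign the patient to the case or control group". Then, "At that point, a message will be sent to activate the patient". The patient follows the link, downloads the app, and there will "receive information about the project and data processing and sign the informed consent if they agree". The courier request for the active group is described after this.

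Other places bear on the same order:

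- Section 2.2 says that all participants receive an SMS link to the app, "from which they will initially electronically sign the informed consent form required to participate in the study". They also give an address for device delivery should they be allocated to the active group.
- The Home app paragraph of section 2.5.1 grants app access to patients who are eligible and have consented.
- Section 2.4 keys the allocation table to a three-digit number in order of inclusion, without defining inclusion. It also states: "The contact details of all patients who electronically sign the informed consent form required to participate will be recorded", for the later follow-up call.
- Table 1 makes willingness to sign the consent form, and to wear the devices if allocated to them, an inclusion criterion.
- Section 2.1 calls the trial single-blind. The only party described as blinded is the endpoint adjudication committee (section 2.5.4).

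**The concern.** Randomisation protects the comparison only if entry to the trial is settled before the arm can be known. Here the allocation exists while four steps are still open: opening the message, downloading the app, reading the information, and agreeing or refusing. Staff recruit on the same platform that makes the allocation, and the arms differ in something patients can value or dislike, namely a smartwatch and an oximeter sent to the home (section 2.5.2).

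If the arm becomes known in that interval, patients may drop out at different rates, or for different reasons, in the two arms. Those who sign would then no longer be comparable groups. The analysis could not readily repair this, because section 2.4 plans follow-up contact only for signers, and the ethics text lets data be kept up to withdrawal for participating patients, which does not clearly cover people who never consented.

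**Working it through.** **Order of steps.** No figure in the plan bears on this point, so the check is to place the passages side by side.

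| Source | Position of consent |
|---|---|
| 2.5.1, integration of modules | After random assignment, after the message, inside the app, with refusal possible |
| 2.2 | Inside the app, reached by SMS link; device delivery is worded as depending on an allocation still to be known |
| 2.5.1, Home app paragraph | Before access to the app |
| 2.4 | Not stated; allocation follows order of inclusion, which is undefined |
| Table 1 | Willingness only, checked at screening before assignment |

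The integration paragraph ties the message to the completed assignment, and section 2.2 confirms that the signature is given in the app reached through that message. On this reading, assignment precedes signature. The Home app paragraph cannot be squared with it: access cannot depend on a consent that is signed inside the app.

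**Possible size.** The article gives no refusal or event rates. Every rate below is an assumption, the true effect is nil, and 250 patients are allocated per arm (the planned number).

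*Scenario A: the control arm is less attractive.* True risk is r = 5% in both arms, decliners' risk is d = 2.5%, and the consent proportion is c. The risk among signers is (r − (1 − c)·d)/c.

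- Active, c = 0.85: (0.05 − 0.15 × 0.025)/0.85 = 0.04625/0.85 = 5.44%
- Control, c = 0.60: (0.05 − 0.40 × 0.025)/0.60 = 0.04/0.60 = 6.67%
- Spurious risk ratio: 5.44/6.67 = 0.82
- Signers: 250 × 0.85 ≈ 212 and 250 × 0.60 = 150

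*Scenario B: consent in the active arm depends on risk.* 30% of patients are high-risk (10% events) and 70% low-risk (2% events). Control consent is 90% throughout, so control risk is 0.3 × 0.10 + 0.7 × 0.02 = 4.4% and signers number 225. With active-arm consent h (high-risk) and l (low-risk), the signers' risk is (0.3·h·0.10 + 0.7·l·0.02)/(0.3·h + 0.7·l).

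| h | l | Active signers | Active risk | Risk ratio |
|---|---|---|---|---|
| 90% | 90% | 225 | 4.40% | 1.00 |
| 90% | 80% | 208 | 4.60% | 1.05 |
| 90% | 70% | 190 | 4.84% | 1.10 |
| 90% | 60% | 172 | 5.13% | 1.17 |
| 70% | 90% | 210 | 4.00% | 0.91 |

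*Scenario C: equal consent does not guarantee absence of bias.* Consent is 80% in both arms and true risk 5%, with decliners' risk 2.5% in active and 7.5% in control.

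- Active: (0.05 − 0.20 × 0.025)/0.80 = 5.63%
- Control: (0.05 − 0.20 × 0.075)/0.80 = 4.38%
- Ratio: 0.05625/0.04375 = 1.29

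The bias is nil only when those who leave have the same effect on risk in each arm.

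**The case against.** The strongest reply is that the article never says anyone learns the arm before signature. It says the platform assigns; the activation message is described in the same way for both arms; and the first arm-specific step, the courier request, comes after consent. A reader might infer that recruiting staff see the arm on their screen beforehand. That is plausible on a shared platform, but it is not in the text. This reply stands, and it makes the bias conditional. It does not remove the point, because no section says the arm is concealed until signature either.

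Table 1 adds a partial safeguard. Willingness to sign and to wear the devices is checked at screening, so some discussion precedes allocation. This makes refusal as high as the 40% assumed for control in scenario A an extreme case. Yet stated willingness is not signed consent, and the workflow explicitly allows refusal later.

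Two further readings are tempting but unsupported:

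- A reader might infer that the exclusion for clinical progression could be applied after allocation. The integration paragraph applies all criteria before the baseline visit and describes no later check. The reading depends on a meaning of inclusion that the article does not give.
- A reader might infer that the table cannot deliver 250 patients per arm. That follows only if the three-digit numbers are used up at registration and refusals are not replaced. The article does not say that the ID issued at registration is that number, and 500 is stated as a maximum.

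**Conclusion.** The point holds in a limited form. The integration paragraph of section 2.5.1 puts random assignment before the in-app information and the signature, and this conflicts with the Home app paragraph and sits badly with section 2.2. As written, patients can decline after allocation, concealment until consent is not described, and follow-up contact is planned only for signers.

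The resulting selection bias is a risk and not a stated fact. It requires the arm to become known before consent and the losses to differ by arm. Where consent differs by arm, the assumed rates give spurious risk ratios from 0.82 to 1.17, so the direction cannot be presumed conservative; the constructed equal-consent case reaches 1.29. None of these rates comes from the article. Refusals would also use up allocation numbers, if those numbers are issued at registration.

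**What to change.** Set one order and use it throughout:

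1. Eligibility check completed.
2. SMS and app download.
3. Project information and time-stamped electronic consent.
4. Issue of the randomisation number by the platform.
5. Notice of the arm and, for the active group, the courier request.

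Define inclusion as consented and then randomised, so that the three-digit number in section 2.4 is consumed only by a consenting patient. Apply no eligibility criterion after randomisation. Bring sections 2.2, 2.4 and both paragraphs of 2.5.1 into line, and state that all randomised patients are analysed in their allocated arm. If any patients were allocated before consent, report their number by arm, including those who then declined.

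The cost is a reordering of platform steps and a short text edit. The courier request is already described after consent, so its place in the sequence does not change.
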